## 5 TRIAL SETTING

This is a single centre research study, taking place in the Department of Psychology, King's College London but the trial is a remote trial and so all testing takes place online (using MS Teams).

## 6 PARTICIPANT ELIGIBILITY CRITERIA

### 6.1 Inclusion criteria

The study is recruiting adults aged 18-35 years. Participants will fall into one of the following categories in order to be eligible for the study:

- i. No current or previous diagnosis of ADHD.
- ii. Current diagnosis of ADHD but not currently receiving any drug treatment for the condition (and have not done so for 3 months).
- iii. Current diagnosis of ADHD and currently receiving psychostimulant drug treatment for the condition with at least 70% adherence.

### 6.2 Exclusion criteria

The exclusion criteria for this study are:

- I. gluten or lactose intolerance, as participants will be asked to ingest a whey protein drink
- II. current or past diagnosis of nutritional, psychiatric (excluding ADHD) or neurological illnesses
- III. being pregnant/breastfeeding
- IV. being a smoker (including e-cigarettes)
- V. currently taking medication known to affect the serotonergic system such as antidepressants

- VI. learning disabilities
- VII. following a restrictive diet (e.g., keto), as this might interfere with the experiment

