## 7 TRIAL PROCEDURES

Participants will first complete a brief online screening survey (~10 mins). As part of the survey, participants will answer question to determine eligibility and provide basic demographic information (e.g., age, gender, ethnicity, education level). The final part of the screening survey that all participants will complete includes a question asking them about any current ADHD diagnosis and the Adult ADHD Self-Report Scale, a short survey assessing ADHD symptomology. For those who report a diagnosis of ADHD, details of treatment (e.g. dose, drug) will be required. Finally, participants will be asked to provide an email address so that they can be contacted by the research team to arrange a time for the testing session once their screening survey answers has been reviewed and they have been confirmed as eligible to participate. All those eligible to participate will be invited to attend a 2-hour online testing session. Given the remote nature of the test, a postal address will also be requested to deliver the protein powder from all eligible participants.

On arrival in the online room, the researcher will remind the participant of the study information and consent will be re-confirmed verbally. Participants will also be asked to confirm that they did not consume protein-rich meals, caffeine, or alcohol the day of the session or the previous night. Participants will then be advised to open the protein powder that had been posted to them and mix the powder with 400 ml of water. They are then asked to put this in the fridge until they are instructed to drink it. The participants will then complete the three cognitive tests. After this they will be asked to drink the protein drink within 10 minutes and then wait a further 1 hour before completing the tests again.

Testing will be in two phases - before and after consuming the protein drink – with the same computerised tests completed in both phases and aim to measure attention and impulsivity. Brief descriptions of the tests are given below:

- Test of attention – participants will be asked to press a letter on a keyboard to respond to a target stimulus whilst inhibiting responses to non-target stimulus.

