### 7.1.2 Screening

All participants are asked to fill in a short online screening survey before they are invited for the laboratory visit to ensure that they meet the eligibility criteria.

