## 7.2 Consent

Informed consent will be taken from all participants twice. As the study involves two parts (an online survey and testing session), written consent is first sought as part of the online survey. Then, consent is re-confirmed verbally at the start of the online testing session. On both occasions, participants are first presented with a written participant information sheet which explains in detail the study and the various tasks the participant will be undertaking (there is a written participant information sheet in the online survey and participants are also given an electronic copy of the information sheet ahead of the test session as part of the booking confirmation). Informed consent is sought by the Research Assistant, who also explains the details of the study to each participant verbally during the online testing session. All participants are encouraged to ask any questions they may have with regards to the study.

Participants can take as long as they need to consider participation in the study, as the information sheet is openly available at the beginning of the online survey, which the participants complete in their own time. At this point, the research team encourages participants to get in touch should they have any questions. If consent is recorded and the participant is eligible to be invited for a lab visit, they will be contacted by the researcher who will schedule the visit at least 5 days apart from the time the online response was recorded (to allow delivery of the protein). Upon arrival in the online room, the Research Assistant checks with each participant if they are still happy to take part in the study.

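### Exclusion I is justified by a whey drink but names only gluten and lactose intolerance; no listed exclusion or described check names allergy to milk or whey protein

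*Protocol*

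**What the plan says.** Protocol section 6.2 lists seven exclusions. The first is tied explicitly to the study drink: "gluten or lactose intolerance, as participants will be asked to ingest a whey protein drink". Two others come near the subject without naming allergy. Criterion II excludes a "current or past diagnosis of nutritional, psychiatric (excluding ADHD) or neurological illnesses", and criterion VII excludes anyone "following a restrictive diet (e.g., keto), as this might interfere with the experiment". The remaining four concern pregnancy or breastfeeding, smoking, serotonergic medication and learning disabilities.

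Section 7.1.2 says participants complete a "short online screening survey before they are invited for the laboratory visit to ensure that they meet the eligibility criteria". At the start of the online session (section 7), "the researcher will remind the participant of the study information and consent will be re-confirmed verbally", and participants are asked to "confirm that they did not consume protein-rich meals, caffeine, or alcohol the day of the session or the previous night". Section 7.2 adds that on both consent occasions "participants are first presented with a written participant information sheet which explains in detail the study", and that consent is sought by the Research Assistant, "who also explains the details of the study to each participant verbally during the online testing session".

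Section 1 (details of supplementation) describes the balanced condition as 40 g of pure whey powder and the low loading condition as having tryptophan added. Section 5 states that all testing is online. Under section 7 the powder is posted, and the participant mixes it with water and drinks it within 10 minutes.

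**The concern.** An exclusion that states its own reason can be tested against that reason. Here the reason is ingestion of whey. Lactose intolerance is a reaction to milk sugar, and gluten intolerance is a reaction to a cereal protein. Whey powder supplies milk protein, and allergy to milk protein is a different condition from either. The criterion therefore misses a hazard that its own justification points to.

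What is at stake is participant safety. A person with a known milk or whey allergy could answer every listed criterion truthfully, be found eligible, and take the drink at home with the researcher present only by video. In a remote design, the eligibility list and the questions asked before the drink are the places to catch this.

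**Working it through.** No formula applies, and the plan gives no figure to reproduce. The check sets the criteria and the described safeguards side by side and asks whether each names allergy to milk or whey protein.

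**Exclusions (section 6.2)**

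| Criterion | Subject | Names milk or whey allergy? |
|---|---|---|
| I | Gluten or lactose intolerance | No |
| II | Nutritional, psychiatric (other than ADHD) or neurological illness | No |
| III | Pregnancy or breastfeeding | No |
| IV | Smoking | No |
| V | Serotonergic medication | No |
| VI | Learning disabilities | No |
| VII | Restrictive diet | No |

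Result: 0 of 7.

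**Screening (sections 7, 7.1 and 7.1.2).** The survey is described as covering eligibility, demographics, ADHD diagnosis, the self-report symptom scale and treatment details. The researcher then confirms eligibility. Both steps work from the section 6.2 list, so a survey built only from that list has the same gap. No allergy question is described.

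**Session-start confirmation (section 7).** The items are protein-rich meals, caffeine and alcohol. Result: 0 of 3 concern allergy.

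**Elsewhere.** The word allergy does not appear in the protocol text available for review.

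**Exposure.** Exclusion I speaks of participants in general taking a whey drink, and section 9.1 plans 48 + 48 + 48 = 144 participants. The 40 g figure is stated for the balanced condition. The low loading condition is described as having tryptophan added, and for the high loading condition only the tryptophan content is given. That all three are whey drinks follows from the wording of exclusion I.

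**Could II or VII do the job?** An allergy is not plainly a nutritional illness. Someone who avoids dairy might or might not regard that as a restrictive diet: the one example given is keto, and the stated reason is interference with the experiment. Each criterion may catch some people with milk allergy, but neither can be relied on to do so.

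**The case against.** The strongest reply is that this is an omission, and that the documents which would settle it are not available. The screening survey and information sheet are the natural place for an allergy question or warning, and the study has ethical clearance (section 12.1). Moreover, only people who know of their allergy are in question. Such a person would read the information sheet at the survey and receive it again with the booking, be contacted by a researcher who confirms eligibility, hear a verbal explanation, be invited to ask questions, re-consent, and still be free to withdraw. Criterion VII can also be read to cover dairy avoidance.

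Much of this stands as mitigation. Many people with a known allergy would probably decline, and the unseen documents may address the point. The session-start confirmation checks same-day and previous-night abstinence and repeats none of the seven exclusions, so the lack of an allergy item there is not a separate failure. The count of 144 is the planned sample, not the number at risk.

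It does not close the gap. If informed consent were enough, the lactose exclusion would not be needed either, yet the protocol includes it. Eligibility is confirmed against the section 6.2 list. If the survey did ask about allergy, that list would still give no stated ground for excluding the person. Eligibility criteria belong in the protocol, so the point cannot be left to a statistical analysis plan.

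**Conclusion.** The concern holds. The scope of exclusion I does not match its stated reason, and none of the 7 exclusions, the described screening steps or the 3 session-start items names allergy to milk or whey protein. The conclusion rests on the criteria and checks as described in the protocol; it makes no claim about the content of the survey or information sheet. The document gives no prevalence, so no number of affected participants is estimated. Sample size, power, outcomes and analysis are unaffected. The change should be made because the hazard is foreseeable and potentially serious and the correction is very cheap.

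**What to change.** - In section 6.2, add to exclusion I, after the two intolerances: *or known allergy or hypersensitivity to milk, whey or any other ingredient of the drink*. Keep the existing reason.
- Make sure the screening survey asks this directly.
- Add the same question to the verbal confirmation at the start of the online session, so that it is re-checked before the drink is taken.

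The cost is one phrase in the criteria, one screening question if it is not already asked, and one verbal check, with at most a few fewer eligible participants. The change will not detect an allergy the participant does not know about.

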## 7 TRIAL PROCEDURES

Participants will first complete a brief online screening survey (~10 mins). As part of the survey, participants will answer question to determine eligibility and provide basic demographic information (e.g., age, gender, ethnicity, education level). The final part of the screening survey that all participants will complete includes a question asking them about any current ADHD diagnosis and the Adult ADHD Self-Report Scale, a short survey assessing ADHD symptomology. For those who report a diagnosis of ADHD, details of treatment (e.g. dose, drug) will be required. Finally, participants will be asked to provide an email address so that they can be contacted by the research team to arrange a time for the testing session once their screening survey answers has been reviewed and they have been confirmed as eligible to participate. All those eligible to participate will be invited to attend a 2-hour online testing session. Given the remote nature of the test, a postal address will also be requested to deliver the protein powder from all eligible participants.

On arrival in the online room, the researcher will remind the participant of the study information and consent will be re-confirmed verbally. Participants will also be asked to confirm that they did not consume protein-rich meals, caffeine, or alcohol the day of the session or the previous night. Participants will then be advised to open the protein powder that had been posted to them and mix the powder with 400 ml of water. They are then asked to put this in the fridge until they are instructed to drink it. The participants will then complete the three cognitive tests. After this they will be asked to drink the protein drink within 10 minutes and then wait a further 1 hour before completing the tests again.

Testing will be in two phases - before and after consuming the protein drink – with the same computerised tests completed in both phases and aim to measure attention and impulsivity. Brief descriptions of the tests are given below:

- Test of attention – participants will be asked to press a letter on a keyboard to respond to a target stimulus whilst inhibiting responses to non-target stimulus.
- Tests of impulsivity – two specific tests will be used to measure impulsivity. In the first test participants will be asked to make choices, using keyboard presses, between hypothetical rewards now or at a point in the future for several different delays e.g. 1 week, 2 weeks, 1 month, 3 months, 6 months and 1 year. In the second test participants will be shown 4 decks of cards (labelled A, B, C, and D) and asked to choose 100 times from the decks with two decks giving greater gains and losses. Additionally, the test of attention will also provide a further measure of impulsivity.

### 7.1 Recruitment

Participants will be recruited through institutional volunteer recruitment channels. The institutional recruitment network at King's is highly effective for recruiting healthy participants and those with conditions such as ADHD (which is relatively common in the student population). However, we will also advertise the study via groups such as the UK Adult ADHD network (<https://www.ukaan.org/otherresearch.htm>) which allows research advertisements and has a long-standing link to King's College and the Institute of Psychiatry, Psychology and Neuroscience. If interested in the study, participants will complete the short

## Study Protocol: Tryptophan and Attention Deficit Hyperactivity Disorder

online questionnaire, after which they will be contacted by the researcher who will confirm eligibility. If eligible, the researcher will contact participants to schedule the online testing session.

### 7.1.1 Participant identification

Potential participants are recruited through (1) advertisements via e-mail circulars, social media platforms and flyers at King's College London, and (2) advertisements via ADHD local/national organisations. The researcher manages all recruitment.

### 7.1.2 Screening

All participants are asked to fill in a short online screening survey before they are invited for the laboratory visit to ensure that they meet the eligibility criteria.

### 7.1.3 Payment

Participants who attend and complete the testing session will receive a £20 Amazon voucher as a 'thank you' for participating.

## 7.2 Consent

Informed consent will be taken from all participants twice. As the study involves two parts (an online survey and testing session), written consent is first sought as part of the online survey. Then, consent is re-confirmed verbally at the start of the online testing session. On both occasions, participants are first presented with a written participant information sheet which explains in detail the study and the various tasks the participant will be undertaking (there is a written participant information sheet in the online survey and participants are also given an electronic copy of the information sheet ahead of the test session as part of the booking confirmation). Informed consent is sought by the Research Assistant, who also explains the details of the study to each participant verbally during the online testing session. All participants are encouraged to ask any questions they may have with regards to the study.

Participants can take as long as they need to consider participation in the study, as the information sheet is openly available at the beginning of the online survey, which the participants complete in their own time. At this point, the research team encourages participants to get in touch should they have any questions. If consent is recorded and the participant is eligible to be invited for a lab visit, they will be contacted by the researcher who will schedule the visit at least 5 days apart from the time the online response was recorded (to allow delivery of the protein). Upon arrival in the online room, the Research Assistant checks with each participant if they are still happy to take part in the study.

## 7.3 Trial assessments

| Intervention or procedure                 | Number of times it is administered | Average time taken per procedure | Person conducting the procedures and where they take place                                                   |
|--------------------------------------------------|-------------------------------------------|-----------------------------------------|---------------------------------------------------------------------------------------------------------------------|
| Online questionnaire (includes informed consent) | 1                                         | 10m                                     | The online questionnaire is hosted on an online survey builder website (i.e., Qualtrics) and can be taken remotely. |
| Informed consent (again, at lab visit)           | 1                                         | 10m                                     | Verbal consent will be sought by a Research Assistant upon arrival in the online room.                              |

## Study Protocol: Tryptophan and Attention Deficit Hyperactivity Disorder

|                                                 |   |     |                                                                                                                                                                                     |
|-------------------------------------------------|---|-----|-------------------------------------------------------------------------------------------------------------------------------------------------------------------------------------|
| Delay Discounting Task (computer-based)         | 2 | 10m | This task is computer-based and performed under monitoring by the Research Assistant during the online testing session. The task is performed before and after protein consumption. |
| Iowa Gambling Task (computer-based)             | 2 | 10m | This task is computer-based and performed under monitoring by the Research Assistant during the online testing session. The task is performed before and after protein consumption. |
| Test of Variables of Attention (computer-based) | 2 | 22m | This task is computer-based and performed under monitoring by the Research Assistant during the online testing session. The task is performed before and after protein consumption. |

Total time to complete the study: approximately 120 minutes including 1 hour break after consumption of the protein drink.

### 7.4 Qualitative assessments

Not applicable.

### 7.5 Withdrawal criteria

Participants are free to withdraw at any point of the study, without having to give a reason. Withdrawing from the study will not affect participants in any way. Participants can withdraw their data up to three months after completion of testing, after which their anonymised data will have been included in analyses and interim reports. If they choose to withdraw from the study, we will not retain the information they have given thus far.

### 7.6 End of study

Participants' involvement with the study ends immediately after completing the second set of cognitive tests and receiving their reimbursement.

## 8 CONCOMITANT MEDICATION

The current study is investigating the effects of tryptophan on ADHD core symptoms in medicated and unmedicated individuals with a diagnosis of ADHD. Participants are instructed to take their medication as usual.

### 8.1 Assessment of medication adherence

While the current study does not involve the administration of any medication, the study is measuring medication adherence of the ADHD medication that some participants are ordinarily taking. This is done in the online screening survey. To measure adherence, participants are asked how many tablets they were supposed to take during the past 2 weeks and how many they took.

## 9 STATISTICS AND DATA ANALYSIS

### 9.1 Sample size calculation

There is no existing data to calculate considering these groups and conditions to sample size. However, similar studies covering components of the current work, indicate small-medium effects sizes, therefore a power analysis assuming this effect size and power of 0.95 was conducted. This suggests that we require a total group size of 144 participants (48 HC, 48 ADHD-M, 48 ADHD-UM).

### 9.2 Planned recruitment rate

Based on availability of researchers to run online testing, we expect to test up to 4 participants per week.

### 9.3 Statistical analysis plan

#### 9.3.1 Primary and secondary outcome analysis

To achieve the study's objectives, we will adopt a 3 x 3 x 2 factorial design. Factor 1, 'ADHD Status', is a between-subjects factor and consists of three distinct participant groups (healthy controls, unmedicated ADHD, medicated ADHD). Factor 2, also between-subjects, is 'Tryptophan modulation' and consists of three conditions: balanced, low loading, high loading. The final factor is within-subjects and is the 'Time' at which measures are collected i.e., before and after protein (tryptophan) consumption. Data analysis will use parametric methods, typically mixed ANOVA, after normality checks and any necessary transformations.

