### 3.6 Table of outcomes

| Objectives                                                                                                                                                                                                                                                        | Outcome Measures | Timepoint(s) of evaluation of this outcome measure (if applicable)                                                                                |
|-------------------------------------------------------------------------------------------------------------------------------------------------------------------------------------------------------------------------------------------------------------------|------------------|---------------------------------------------------------------------------------------------------------------------------------------------------|
| Primary Objective: To assess the impact of tryptophan loading on attention and impulsivity in adults with ADHD, both alone and in combination with ADHD medication (psychostimulants or non-stimulants) with a healthy control (non-ADHD) reference group. | TOVA, DDT, IGT   | Tests will be conducted before tryptophan loading at the start of the laboratory session and again 1 hour after consumption of the protein drink. |

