## 4 TRIAL DESIGN

Double blind randomised controlled trial with randomisation stratified by group (ADHD-M, ADHD-UM, HC) and gender (male female) into three different tryptophan conditions, creating a 3 (participant group) x 3 (tryptophan modulation) x 2 (time, before and after) design.

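### Putting the pre-drink score into a within-subjects Time factor makes the tryptophan test a change-score test: valid, but less precise than adjusting the post-drink score for baseline

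*Protocol*

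**What the plan says.** Section 4 of the protocol describes randomisation to three tryptophan conditions, stratified by participant group and gender, "creating a 3 (participant group) x 3 (tryptophan modulation) x 2 (time, before and after) design". Section 3.6 sets the timing: "Tests will be conducted before tryptophan loading at the start of the laboratory session and again 1 hour after consumption of the protein drink". Every participant who completes the session therefore has a pre-drink and a post-drink score on each task.

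Section 9.3.1 turns this into an analysis. Of tryptophan it says: "Factor 2, also between-subjects, is 'Tryptophan modulation' and consists of three conditions: balanced, low loading, high loading". Of time it says: "The final factor is within-subjects and is the 'Time' at which measures are collected i.e., before and after protein (tryptophan) consumption". The model is given in one sentence: "Data analysis will use parametric methods, typically mixed ANOVA, after normality checks and any necessary transformations". The pre-drink score is thus half of a repeated outcome. No baseline-adjusted model is named, and the term that tests tryptophan is not identified.

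Section 9.1 gives 144 participants, 48 per participant group. It says that similar studies "indicate small-medium effects sizes" and that "therefore a power analysis assuming this effect size and power of 0.95 was conducted". It states no numerical effect size, alpha, pre-post correlation, standard deviation or allocation ratio.

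**The concern.** A pre-drink score cannot be affected by the drink. Its only use in a randomised comparison is to explain variation in the post-drink score. A change score subtracts the whole of it, which amounts to assuming a regression slope of 1 of post on pre. ANCOVA estimates that slope from the data. Unless the true slope happens to be 1, the change score carries avoidable noise.

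This matters more where cells are small. Section 1 asks about unmedicated and medicated ADHD separately, and 48 per group over three conditions is 48/3 = 16 per cell if allocation is equal. Precision is also costly to obtain by recruitment. Section 9.2 expects up to 4 participants a week. If ρ were 0.5 with equal SDs, a change-score analysis would need 144/0.75 = 192 participants to match ANCOVA on 144. That is 48 more people, or at least 12 more weeks. The pre-drink scores that supply this precision are already being collected.

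**Working it through.** **Inputs from the protocol.** N = 144, 48 per participant group (9.1); three randomised tryptophan conditions (4, 9.3.1); two time points (3.6, 9.3.1).

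**Assumed, because the protocol does not state them.** ρ from 0.3 to 0.7, with 0.8 and 0.9 also shown; equal pre and post SDs, then SD ratios of 0.8 and 1.25; equal allocation (16 per cell, 48 per tryptophan condition); two-sided alpha 0.05; and, for illustration only, a true difference of d = 0.5 SD.

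**1. The plan's own figure.** The 144 at power 0.95 cannot be uniquely reproduced, because the effect size f, alpha, ρ and the tested term are all missing. It is compatible with a small-to-medium effect:
- nine cells with f = 0.25 and ρ = 0.3 (an 8 df interaction with time) gives 144;
- group × tryptophan × time (4 df) at ρ = 0.5 reaches 0.95 with f = 0.183;
- tryptophan × time (2 df) at ρ = 0.5 reaches 0.95 with f = 0.166.

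The figure is neither confirmed nor shown to be wrong.

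**2. Tryptophan × time is the change-score test.** In one simulated data set of 144 with the 3 × 3 × 2 layout, the split-plot tryptophan × time F was 0.7106. The tryptophan F from an ANOVA of change was also 0.7106. The within-subject mean square (0.5018) was exactly half the change-score mean square (135.483/135 = 1.0036), both on 135 df.

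**3. Variance with equal SDs (σ).**
- Change score: 2σ²(1 − ρ).
- ANCOVA residual: σ²(1 − ρ²).
- Ratio ANCOVA/change: (1 + ρ)/2. Reduction: (1 − ρ)/2.

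| ρ | Change (σ²) | ANCOVA (σ²) | Ratio | Reduction |
|---|---|---|---|---|
| 0.3 | 1.4 | 0.91 | 0.65 | 35% |
| 0.5 | 1.0 | 0.75 | 0.75 | 25% |
| 0.7 | 0.6 | 0.51 | 0.85 | 15% |
| 0.8 | 0.4 | 0.36 | 0.90 | 10% |
| 0.9 | 0.2 | 0.19 | 0.95 | 5% |

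Simulation (4000 runs per ρ, N = 144) gave reductions of 36%, 24% and 13% at ρ = 0.3, 0.5 and 0.7. Allowing one degree of freedom for the covariate, the formula gives about 34.5%, 24.4% and 14.4%.

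**4. Unequal SDs.** With s = SDpost/SDpre, the reduction is 1 − s²(1 − ρ²)/(s² + 1 − 2ρs), which simplifies to (1 − ρs)²/(s² + 1 − 2ρs). At ρ = 0.5:
- s = 0.8: 0.36/0.84 = 43%;
- s = 1: 0.25/1 = 25%;
- s = 1.25: 0.1406/1.3125 = 11%.

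The numerator is a square, so apart from the small degrees-of-freedom cost the reduction is never negative. It is zero only when ρs = 1, the case where the slope of post on pre is 1.

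**5. Illustrative pairwise power (d = 0.5, ρ = 0.5, equal SDs).** The noncentrality is 0.5/√(2v/n), with v = 1.0 for change scores (135 df) and v = 0.75 for ANCOVA (134 df).

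| Comparison | n v n | Change: noncentrality, power | ANCOVA: noncentrality, power |
|---|---|---|---|
| One ADHD group | 16 v 16 | 1.414, 0.29 | 1.633, 0.37 |
| Both ADHD groups | 32 v 32 | 2.000, 0.51 | 2.309, 0.63 |
| All groups | 48 v 48 | 2.449, 0.68 | 2.828, 0.80 |

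With group-specific slopes (132 df) the ANCOVA powers are the same to two decimals.

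**The case against.** The strongest reply is that nothing here is an error of validity. Tryptophan is randomised within strata, so the change-score contrast is unbiased with correct type I error. That stands, and it limits the point to efficiency. A reader might go further and argue that change scores mishandle the chance baseline differences between cells of 16, whose standard error is √(2/16) = 0.354 SD. That variation is already in the change-score standard error, so it is not a second problem.

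The word "typically" in section 9.3.1 leaves some room, and a statistical analysis plan that is not shown could name a covariate. The room is partial: the protocol itself fixes Time as a factor in both section 4 and section 9.3.1.

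A reader might take 15–35% as a property of this trial. The documents do not support that. They give no correlation and no SDs. Both testing rounds fall in one session, so ρ of 0.8 or 0.9, with a gain of only 10% or 5%, is possible. A low ρ would make the gain larger, up to 50% at ρ = 0. The measures may also differ from one another in ρ and in SD ratio.

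A reader might also infer that the tryptophan main effect, which averages an unaffected pre-drink score with the post-drink score and so halves the effect, is the planned test. The protocol does not say so, and a design with a time factor points more naturally to the interaction with time.

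Finally, the illustrative powers might be read as proof that 144 is inadequate. They rest on a d, an alpha and an allocation that section 9.1 does not state, and on pairwise comparisons that it does not name as the basis of the calculation. They compare two analyses of the same data and nothing more.

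**Conclusion.** The point holds as a loss of precision. The analysis in section 9.3.1 tests tryptophan through change scores although a more precise unbiased analysis of the same data is available. The direction is certain in large samples. The size depends on assumptions: it is (1 − ρ)/2 with equal SDs, so moderate at mid-range correlations and slight at high ones, and it moves with the SD ratio. The gain belongs to the randomised tryptophan contrasts, overall and within each participant group. It should not be claimed for main-effect comparisons between healthy, unmedicated and medicated participants, who are not randomised to those groups. The change is worth making because it costs almost nothing.

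**What to change.** In section 9.3.1, name as the primary test of tryptophan, for each outcome, an ANCOVA of the post-drink score on tryptophan condition, participant group, their interaction, and the pre-drink score of the same measure. Centre the pre-drink score within participant group and allow a group-specific slope, because the groups are not randomised and may differ at baseline. Where an outcome is transformed, apply the same transformation to both scores. Report adjusted loading-minus-balanced differences with confidence intervals, and keep the 3 × 3 × 2 mixed ANOVA as a supportive analysis.

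The cost is a change of wording and one degree of freedom for a common slope, or three for group-specific slopes, out of 135. No extra data, visits or participants are needed.
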